### Procedure

There will be two groups in this study. Participants in group A will receive the ReNACE psychoeducational intervention while the participants in group B, belonging to the control group, will be given a general educational programme.

Allocation will be made according to the centre in which participants are attended. The experimental intervention was assigned to the centres in a random draw by tossing a coin (heads-control, tails-experimental) [27]. In this study individual randomisation, that is by patient or family carer, is not feasible because there is a high risk of contamination between intervention and control groups when participants interact with each other during their visits to their health centre. This is due to the patients from each health centre usually have the same family physician and nurse, and live in the same neighborhood. We decided to choose the six health centres with the highest numbers of people diagnosed with PD. With this proposed allocation strategy it is expected that contamination between the control and intervention groups will be minimal.

Furthermore, participants will be blinded to intervention assignment [28] as they will only be aware of the intervention they are receiving and they will not know if they belong to the intervention or control group. The healthcare professionals helping the participants in data collection will also be blinded to intervention assignment [28]. The healthcare professionals delivering the sessions to all the participants in the control and intervention groups will always be the same.

### The intervention

The group A will participate in the ReNACE psychoeducational intervention for 9 weeks with one 90 min group session per week. The objective of the contents of this intervention is to foster the coping skills of the participants to facilitate and promote their psychosocial adjustment to PD. The sessions will take place in groups of 15–20 people at most so as to promote reflection and facilitate the interchange of opinions between participants about issues of interest from their day to day experience of coping with PD. Table 3 shows the organisation of the topics that will be dealt with in each weekly session.

**Table 3 Tab3:** Summary of the ReNACE psychoeducational intervention. Intervention group (A)

	Target audience	Topic	Provider
Session 1	Patients	Global introduction to the intervention	General practitioner
	Carers	Global introduction to the intervention	General practitioner
Session 2	Patients	Getting to know Parkinson’s disease	Neurologist
	Carers	Healthy life habits	Primary Care nurse
Session 3	Patients	Healthy life habits	Primary Care nurse
	Carers	Getting to know Parkinson’s disease	Neurologist
Session 4	Patients	Resources	Social worker
	Carers	Management of stress and complicated situations	Psychologist
Session 5	Patients	Adapting to and coping with Parkinson’s disease	General practitioner and Expert patient
	Carers	Resources	Social worker
Session 6	Patients	Positive self-esteem *&* Empathy and patience	Psychologist
	Carers	Look for information and live in the present *&* Normalise the situation and partake in activities	Psychologist
Session 7	Patients	Management of stress and complicated situations	Psychologist
	Carers	Positive self-esteem *&* Empathy and patience	Psychologist
Session 8	Patients	Look for information and live in the present *&* Normalise the situation and partake in activities	Psychologist
	Carers	Adapting to and coping with Parkinson’s disease	General practitioner and Expert patient
Session 9	Patients	Conclusions	General practitioner
	Carers	Conclusions	General practitioner

The main focus of the intervention is on empowering participants’ coping skills with stressful situations, which could clearly cause a crisis in the positive living with a LTC like PD [21]. This approach seeks that the participants become aware of their cognitive and behavioural efforts, think about them, and choose those that help them better adjust to PD [14]. In particular, professionals will work with the meaning of coping with PD explained by Navarta-Sánchez et al. [14]. All sessions will take place on the same day with the people with PD and their family carers, but in separate groups (see Table 3). This has been planned so as to prevent patients from not expressing themselves freely for fear of hurting the feelings of their family carers and vice versa. At the same time, as is shown in Table 3, the intervention will be delivered by a multidisciplinary team with years of clinical experience working with people with PD and other LTCs. All professionals of this team will use a manual which contains a description of the content and methodology of each session in order to improve adherence to intervention’s characteristics.

Furthermore, in one of the sessions a person with PD and a long history of the disease and a great interest in helping other people with PD to better cope with their situation will participate. Precisely with this objective, this person wrote a book, which will be offered for free as supportive written material to the participants. Also, in all the sessions participants will receive a document summarising the content covered and presented during the session on a projection screen.

The attendance of participants will be controlled in all sessions so that these data are available for analysis of the results. Those participants not attending at least 70% of the intervention sessions will be counted as lost to the study. Bearing in mind the complexity of the recruitment process and the duration of the interventions, it is expected that the interventions will need to be delivered over a period of 18 months.

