### Participants

Participants will be people with PD receiving care as outpatients in the designated centres, over the age of 18 years, in any stage of the disease (as determined by a researcher with the Hoehn & Yahr scale [22]), residing at that time in Navarra, fluent in the speaking and understanding of the Spanish language, and with preserved cognitive ability (as determined by medical history or the doctor responsible).

Family members/carers will be over the age of 18, living or maintaining a close relationship with the patient and actively collaborating in his/her care, currently residing in Navarra and fluent in the speaking and understanding of the Spanish language.

Individuals with PD may enter the research project even though they do not have a family carer or the carer does not wish to participate. The family carer will also be able to enter the research project even though the individual with PD cannot participate for not meeting the inclusion criteria or for lack of interest.

Any change in participants’ circumstances during the study which mean that they do not meet the inclusion criteria mentioned above will cause the discontinuation of the participants in the study.

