### The control group

The general educational programme for the control group or group B (see Table 4) will last 5 weeks with a 90 min group session each week.

**Table 4 Tab4:** Summary of the general educational program. Control group (B)

	Target audience	Topic	Provider
Session 1	Patients	Introduction	General practitioner
	Carers	Introduction	General practitioner
Session 2	Patients	Parkinson’s disease	Neurologist
	Carers	Habits for a healthy life	Primary Care nurse
Session 3	Patients	Habits for a healthy life	Primary Care nurse
	Carers	Parkinson’s disease	Neurologist
Session 4	Patients	Resources	Social worker
	Carers	Resources	Social worker
Session 5	Patients	Conclusions	General practitioner
	Carers	Conclusions	General practitioner

The objective of this programme is to provide participants with general information about PD, healthy lifestyles, and the resources available in the community. Through this intervention participants will be provided with the information generally received from social and healthcare professionals in usual care. The participants will receive this information in group sessions in order to simulate the effect of social interaction that may occur between the participants of the intervention group. It is estimated that the number of people attending each session will be between 15 and 20 at most. The issues that will be dealt with in each session are presented in Table 4. All sessions will take place on the same day with the patients and their family carers but in separate groups in separate rooms for the same reasons as described in the previous section. Attendance to the sessions will be registered as explained above.

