### Data analysis

#### Quantitative data

Analysis of quantitative data will be performed on an intention to treat basis and for that SPSS version 23.0 will be used. A descriptive analysis of the sociodemographic data will be made. For the quantitative variables, means and standard deviations will be calculated. Mixed ANOVA within-pairs and between-pairs to compare patients with family carers at each measurement points, unpaired student t tests to determine any significant differences between the two groups at baseline (T0) and the measurements at T1 and T2 will be used. Also, a mixed factorial ANOVA with 1 between-subjects factor with 2 levels (intervention and control), and 1 within-subjects factor with 3 levels (baseline, time 1 post-intervention, time 2 post-intervention) will be used to compare differences between the two groups in the main variables over time. If any demographic variable result different will be use as a covariate in this analysis.

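### Counting participants with under 70% attendance as lost contradicts the stated intention-to-treat analysis, and the rule's reach in the control group is not stated

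*Protocol article*

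**What the plan says.** All references are to the protocol article.

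- **Data analysis, Quantitative data:** "Analysis of quantitative data will be performed on an intention to treat basis". The main comparison is a mixed factorial ANOVA with two groups and three time points (T0, T1, T2). Unpaired t tests of the groups at each time point are planned as well.
- **The intervention:** "Those participants not attending at least 70% of the intervention sessions will be counted as lost to the study". Group A meets "for 9 weeks with one 90 min group session per week".
- **The control group:** the programme "will last 5 weeks with a 90 min group session each week". On attendance it says only: "Attendance to the sessions will be registered as explained above". It does not repeat the 70% rule or say that the rule applies.
- **Procedure:** "Allocation will be made according to the centre in which participants are attended". The allocated arm of any participant is therefore the arm of their centre.
- **Participants:** a later change that breaks an inclusion criterion "will cause the discontinuation of the participants in the study".
- **Limitations:** the article expects that losses could be above the usual level, and ties this to the participants' age and physical state.

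**The concern.** Intention to treat means that people are analysed as allocated, whatever they then do. A rule that treats low attenders as lost conditions the analysed set on something that happens after allocation. Both statements can stand only if those participants are still measured at T1 and T2 and still analysed, and the article does not say so.

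The planned model makes this matter. A conventional repeated-measures ANOVA uses people with all three measurements. Someone recorded as lost after the sessions has no T1 or T2 value and drops out of it.

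The selection is unlikely to be neutral. On the article's own account, losses are expected to go with age and physical condition, and both plausibly relate to quality of life in a progressive disease. The two programmes also differ in length and content, so staying above 70% is a different test in each. At stake is whether the primary comparison, reported as intention to treat, is in fact a comparison of attenders.

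**Working it through.** **1. The plan's own sample size, for context.** Inputs from Table 2: SD 15.44 and difference 10 (patients); SD 25.04 and difference 15 (carers); power 80%; losses 25% and 20%. Two-sided alpha of 0.05 is assumed because none is stated. With n = 2(1.96 + 0.842)² SD²/d² per group:

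- Patients: 37.4, so 38, and 38/0.75 gives 51. The t-test version gives 39, and 39/0.75 = 52, as stated.
- Carers: 43.7, so 44, and 44/0.80 = 55. The stated 53 matches 44 × 1.20 = 52.8.

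The stated sizes are reproduced closely enough, and this point alleges no error in them.

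**2. What 70% means in sessions.** Group A: 0.70 × 9 = 6.3, so at least 7 of 9 (78%). Group B, if the rule applies: 0.70 × 5 = 3.5, so at least 4 of 5 (80%).

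**3. Share counted as lost.** The documents give no attendance rates, so these are assumptions over a range.

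Equal, independent attendance with probability p per session; lost = P(X ≤ 6 of 9) in A and P(X ≤ 3 of 5) in B:

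| p | A | B |
|---|---|---|
| 0.70 | 53.7% | 47.2% |
| 0.75 | 39.9% | 36.7% |
| 0.80 | 26.2% | 26.3% |
| 0.85 | 14.1% | 16.5% |
| 0.90 | 5.3% | 8.1% |

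Stopping for good with probability h before each session; lost = 1 − (1 − h)⁷ in A and 1 − (1 − h)⁴ in B:

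| h | A | B |
|---|---|---|
| 2% | 13.2% | 7.8% |
| 5% | 30.2% | 18.5% |
| 10% | 52.2% | 34.4% |

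If the rule applies to group A only, the loss in B from this rule is zero.

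**4. Reading the tables.** The sign of the difference between arms changes with the assumed pattern. Equal loss rates would not make the retained groups comparable either, because each is selected on a different programme.

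**5. An illustrative simulation with no treatment effect.** Assumed: log-odds of attendance 1.8 at first, falling 0.15 per week and 0.6 lower per SD of worse prognosis; prognosis correlated 0.6 with PDQ-39 at both T0 and T1; SD 15.44. About 60% of A and 73% of B are retained. The retained arms differ by about 1.5 to 1.6 points in T1 level in favour of A. About 1.5 points of that is already present at T0, and the difference in change is under 0.1 point. Under these assumptions the selection shows as a baseline imbalance, not as a difference in change. A bias in change would need prognosis to predict deterioration, on which the documents give nothing.

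**The case against.** The best defence is the data collection text under Outcome measures. People who miss the T0 or T1 appointment are telephoned and sent the questionnaire by post, and at T2 it is posted to all participants. On that reading the loss rule is only an attendance label and follow-up continues. This shows that the means of following low attenders exist. It does not say that a person counted as lost still belongs to those followed or analysed, and the plain sense of the attendance rule is the opposite.

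Other objections succeed against stronger readings that a reader might infer:

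- **That group A is filtered more heavily and the result is biased towards ReNACE.** Not supported. The tables above go both ways, and in proportion the threshold is slightly stricter in B.
- **That the bias can be given in PDQ-39 points.** Not supported. The simulated gap is in level, whereas the stated primary outcome is improvement compared with the change in controls. The planned t tests at T1 and T2 would show a level gap, but they are not that comparison.
- **That the rule alone uses up the planned loss allowance.** The 26% loss needs an assumed 0.80 attendance. The 25% and 20% allowances come from earlier studies and may already include people who stop attending.
- **That the eligibility-change clause contradicts intention to treat in the same way.** It does so only if discontinuation removes data from the analysis, which the article does not settle. There is also a fair question whether self-report scores remain valid once a patient's cognition is no longer preserved, or a carer no longer cares.

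**Conclusion.** The contradiction between the attendance rule and the intention-to-treat statement stands. It lies in the current text, so a later analysis plan could resolve it only by overriding one of the two sentences. It concerns the analysed set for the primary outcome and should be resolved before the quantitative analysis.

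Two further things follow. The article leaves open whether the rule covers group B. And because the programmes differ in length and content, the retained groups may not be comparable even if it does. That the selection is informative rests on the article's own link between losses, age and physical condition, and is plausible rather than shown. The size and direction of any bias cannot be determined from the documents.

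**What to change.** Reconcile the sections on the intervention, the control group and the quantitative analysis:

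1. State that every enrolled participant is invited to T1 and T2 through the existing appointment and postal process, whatever their attendance.
2. State that all available data are analysed by the allocation of the participant's centre.
3. Keep the 70% attendance set only for a labelled per-protocol or adherence sensitivity analysis, with the same stated rule in both groups.
4. Clarify that discontinuation after a change in eligibility does not remove data already collected from the analysis.
5. Recruitment began in March 2015 and the article describes 30% of the study as still to be completed. Any T1 data not collected from earlier low attenders cannot be recovered and should be reported as missing.

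The cost is wording and a small amount of extra follow-up. The effect estimate may be diluted. Treating participants as independent, with two-sided alpha of 0.05, power = Φ(d(1 − f)/(SD√(2/n)) − 1.96), where f is an assumed dilution of the effect:

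| f | Patients, n = 52 per group | Carers, n = 53 per group |
|---|---|---|
| 0 | 91% | 87% |
| 10% | 84% | 79% |
| 20% | 75% | 69% |
| 25% | 70% | 64% |

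These figures assume that everyone is measured. Actual questionnaire losses would lower them.

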### The control group

The general educational programme for the control group or group B (see Table 4) will last 5 weeks with a 90 min group session each week.

**Table 4 Tab4:** Summary of the general educational program. Control group (B)

	Target audience	Topic	Provider
Session 1	Patients	Introduction	General practitioner
	Carers	Introduction	General practitioner
Session 2	Patients	Parkinson’s disease	Neurologist
	Carers	Habits for a healthy life	Primary Care nurse
Session 3	Patients	Habits for a healthy life	Primary Care nurse
	Carers	Parkinson’s disease	Neurologist
Session 4	Patients	Resources	Social worker
	Carers	Resources	Social worker
Session 5	Patients	Conclusions	General practitioner
	Carers	Conclusions	General practitioner

The objective of this programme is to provide participants with general information about PD, healthy lifestyles, and the resources available in the community. Through this intervention participants will be provided with the information generally received from social and healthcare professionals in usual care. The participants will receive this information in group sessions in order to simulate the effect of social interaction that may occur between the participants of the intervention group. It is estimated that the number of people attending each session will be between 15 and 20 at most. The issues that will be dealt with in each session are presented in Table 4. All sessions will take place on the same day with the patients and their family carers but in separate groups in separate rooms for the same reasons as described in the previous section. Attendance to the sessions will be registered as explained above.

### Outcome measures

#### Quantitative data collection

The primary outcome is the improvement in quality of life of the people with PD and of the family carers participating in the ReNACE psychoeducational intervention, in comparison with the change observed in the quality of life of those participating in the general educational programme. The secondary outcomes will be the changes in the coping skills and in the psychosocial adjustment to PD. These outcomes will be measured in the control and intervention groups at 3 time points; baseline (T0); immediately after the end of the intervention (T1); and 6 months post-intervention (T2). To ensure blinding of the groups and the intervention, researchers involved in data collection will not have participated in any of the group sessions and known the group allocation. At baseline (T0) the sociodemographic data of the participants will be collected. At the three time points the following instruments will be used to measure the outcomes:

Patients:The Quality of Life Scale in Parkinson’s disease (PDQ-39) [29, 30]The Psychosocial Adjustment to Illness scale (PAIS-SR) [31]The Brief COPE scale [32, 33]

Family carers:The Scale of Quality of Life of Care-givers (SQLC) [23, 34]The Psychosocial Adjustment to Illness scale (PAIS-SR) [31]The Brief COPE scale [32, 33]

The measurement scales selected are validated instruments which furthermore, have been used previously in a study of the ReNACE programme in PD patients and their family carers [11].

It is calculated that the participants will need approximately 1 hour to complete the questionnaires. When the participants finish the questionnaire, the researcher will check that they have been filled in correctly in order to minimise data loss.

To favor the collection of data at the most appropriate moment, participants will be given an appointment in their local centre to answer the questionnaires at T0 and T1. If participants do not attend these meetings they will be contacted by telephone to explain that the questionnaire will be sent by postal mail and that they should hand it in the centre or send it in the stamp addressed envelope within the period of 1 week. Furthermore, they will be given a telephone number that they can ring should they have any doubts about the questionnaire. For the evaluation of the results at T2 (6 months post-intervention) the questionnaires will be sent by post to all the participants and the same process as described above will be followed for their collection.

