## Methods

### Aim

The aim of this present study is to improve the quality of life of people with PD and their family carers by means of a multidisciplinary psychoeducational intervention focusing on fostering coping strategies and their psychosocial adjustment to PD. The study also seeks to compare the effectiveness of the psychoeducational intervention focusing on the acquisition of coping skills with a control group receiving a general educational programme. The study will evaluate the perceptions, opinions and satisfaction of the patients and family carers who receive the psychoeducational intervention and will explore the reflections of the social and healthcare providers involved in this intervention.

On the basis of previous research [9–14, 18], the hypothesis we propose is that through the development of coping skills which will contribute to promoting a positive psychosocial adjustment to PD, the quality of life of the people with PD and their family carers will be improved. And the second hypothesis we suggest is that this psychoeducational intervention will enhance the quality of life of the patients and family carers more than a general education programme.

If we find significant results in this psychoeducational approach, we consider that at the long-term, this could develop larger scale interventions and have positive effects on the overall health of patients and their family carers. In particular, we expect that, by integrating psychoeducational interventions into care pathways, the patients and family carers will perceive a greater sense of normality in their lives [4, 10, 12, 21], which will also promote compliance with drug treatments and healthy lifestyles and professionals would be able to identify and support cases with poor illness management and coordinate levels of care more efficiently.

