### Sample size

For the quantitative data collection, the sample size necessary to detect medium to large differences in the primary outcome of the project, quality of life, was calculated. To this end, a previous study of the ReNACE programme [11] with patients with PD and family carers was taken as a reference point together with previous studies [13, 23], using the quality of life scales that will be used in this study in people with PD and family carers. Furthermore, previous research on patients [19, 24] and family carers [25] has been taken into account to calculate the percentage of losses expected during follow-up. Calculation of the sample size was performed using the statistical programme STATA for both control and intervention groups. The parameters used for the calculation of the sample size are shown in Table 2.

**Table 2 Tab2:** Parameters used for the calculation of the sample size by group

	Mean (SD) Quality of life	Size effect. Clinically significant difference	Power	Expected losses over follow-up	Ideal sample size
Patients	29.03 (15.44)^a^	10	80%	25%	52
Carers	104.70 (25.04)^b^	15	80%	20%	53

SD: standard deviation

^a^Questionnaire on Parkinson’s disease PDQ-39 of Peto et al. (1995) [26]

^b^Scale of Quality of Life of Care-givers SQLC of Glozman et al. (1998) [31]

The minimum sample size calculated is 52 patients and 53 family carers for the intervention group and the same for the control group. Therefore, the study will require a minimum of 104 patients with PD and 106 family carers.

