Furthermore, as in the majority of previous interventions [20, 24, 40, 42], it is expected that with the ReNACE psychoeducational intervention statistically significant results will be obtained in the short-term, immediately after the end of the intervention. As for the evaluation of long-term results, in most of the studies conducted no statistically significant long-term results were obtained [20, 42] or they were not evaluated [19, 24, 41]. This shows the complexity involved in enabling people with PD to continue coping with the new situations that they will encounter when living with this neurodegenerative disease once the intervention period has finished but the progression of the disease and its consequences continues. However, the results of two randomised controlled trials into PD [13, 40] and a systematic review in LTCs [43] suggest that interventions focusing on improving lifestyles, redefinition of biography, social networks, emotional wellbeing and activities of daily life, such as the ReNACE intervention (see Table 3), represent tools with a great potential to help people with LTCs to know in the long-term how to deal with the difficulties caused by living with the disease. Specifically, considering the dynamic nature of the process of coping and adjustment to PD, this is where Primary Care professionals could play a vital role because if we demonstrate that these types of interventions are effective and feasible through projects, its continuation and reinforcement from a clinical perspective in the community will be the next step for the long term sustainability of the improvements and transformation of care pathways.

Furthermore, it is worth noting the small number of studies that have taken into account the need to train the family carers of patients with PD. However, there is an increasing number of authors [9–11, 36] who underline the importance of engaging family carers in a training process that allows them to better cope with the experience of the LTC. For this reason, in the quasi-experiment that we propose, the family carers will receive sessions with information suitable for their needs and this will clearly contribute to one of the big gaps in the literature when it comes to educating and caring from PD patients and family carers as a family unit.

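### Quality of life, the primary outcome, is tested three overlapping ways in each of two populations, and no test or time point is named as deciding

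*Protocol article*

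**What the plan says.** Under Outcome measures (Quantitative data collection), the protocol article says: "The primary outcome is the improvement in quality of life of the people with PD and of the family carers" in the intervention group, set against the change seen in the general educational programme. Patients are measured with PDQ-39 and carers with SQLC, and neither population is ranked above the other. On timing it says: "These outcomes will be measured in the control and intervention groups at 3 time points". No time point is singled out.

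Under Data analysis (Quantitative data), the plan lists "unpaired student t tests to determine any significant differences between the two groups at baseline (T0) and the measurements at T1 and T2". It adds a mixed factorial ANOVA with two groups and three times, which "will be used to compare differences between the two groups in the main variables over time". Neither analysis is called primary, and there is no rule for combining the results.

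Sample size, Table 2, gives one two-group calculation per population.

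The Aim section begins its outlook on wider use with "If we find significant results in this psychoeducational approach". The Discussion expects that "statistically significant results will be obtained in the short-term, immediately after the end of the intervention", and notes that most earlier studies found no significant long-term results or did not evaluate them.

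**The concern.** Each population gets three tests of essentially one question: arm difference at T1, arm difference at T2, and group-by-time interaction. If any of them may support the conclusion, the chance of a spurious finding exceeds the level of a single test.

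The tests also do not answer the same question. The primary outcome is a difference in change. The t tests compare levels, so they carry any baseline difference between arms, and the Limitations section itself names baseline differences between centres as possible. The ANOVA interaction does address change, but it is an omnibus test: a significant result does not say at which time, or in which direction, the arms differ.

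The authors expect a short-term effect and report that long-term effects have rarely been shown, so a split result at T1 and T2 is foreseeable. The document does not say what would then be concluded about the primary outcome.

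**Working it through.** **1. Reproduce Table 2, to infer alpha.** "The parameters used for the calculation of the sample size are shown in Table 2", but alpha and sidedness are not among them. The inputs are: patients SD 15.44, difference 10, losses 25%; carers mean (SD) "104.70 (25.04)^b", difference 15, losses 20%; power 80%.

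Formula: n per group = 2(z₁₋α/₂ + z₀.₈₀)² × (SD/difference)². With two-sided 5%, (1.960 + 0.842)² = 7.849.

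- Patients: 2 × 7.849 × 1.544² = 37.4, so 38; 38/0.75 = 50.7, so 51. The t-based version gives 39, and 39/0.75 = 52, as stated.
- Carers: 2 × 7.849 × 1.669² = 43.7, so 44; 44/0.80 = 55, and 44 × 1.2 = 52.8, so 53, as stated.
- One-sided 5% gives 40 and 44 per group, against the stated 52 and 53.

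Two-sided 5% therefore reproduces Table 2 approximately and is used below as an assumption.

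**2. Expected completers per arm.** Patients: 52 × 0.75 = 39. Carers: 53 × 0.80 = 42.4, taken as 42.

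**3. Reference values if tests were independent.** Two tests: 1 − 0.95² = 9.75%. Six tests: 1 − 0.95⁶ = 26.5%. The planned tests share data, so simulation is needed.

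**4. Simulation under no effect.** There were 10,000 runs per setting, with independent individuals. The tests were the t test at T1, the t test at T2 and the group-by-time F test, each at 5%. Assumed, because the documents do not give them: within-person correlation 0.5, 0.7 and 0.85; patient–carer correlation 0, 0.3 and 0.5. The baseline t test and the patient-versus-carer ANOVA are not tests of benefit and were not counted. A selection of settings (%):

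| Within-person r | Patient–carer r | Any of three, patients | Any, either population | In favour, patients | In favour, either population |
|---|---|---|---|---|---|
| 0.5 | 0 | 12.7 | 24.1 | 6.3 | 12.6 |
| 0.5 | 0.5 | 12.4 | 22.0 | 6.9 | 11.8 |
| 0.7 | 0 | 12.0 | 23.3 | 6.2 | 12.1 |
| 0.7 | 0.5 | 12.3 | 21.6 | 6.5 | 11.6 |
| 0.85 | 0 | 11.6 | 22.3 | 5.6 | 11.3 |
| 0.85 | 0.5 | 11.9 | 21.1 | 6.1 | 11.1 |

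Over all nine settings, any of three in patients ran from 11.6% to 12.9%. A repeat with 39 or 42 completers gave 11.3% to 13.0%. The interaction test alone stayed at 4.8–5.4% in patients, and at 9.1–10.1% if either population could succeed on it.

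**5. Cost of splitting alpha across the two populations.** With one test per population at 2.5%, (2.241 + 0.842)² = 9.505.

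- Patients: 2 × 9.505 × 1.544² = 45.3, so 46; 46/0.75 = 61.3, so 62 per group.
- Carers: 2 × 9.505 × 1.669² = 53.0, so 53; 53/0.80 = 66.3, so 67 per group.
- Totals: 124 patients and 134 carers, against the stated 104 and 106. At the planned size, power is about 73% and 70%.

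**The case against.** The strongest reply is that the document does point to a deciding analysis. The primary outcome is defined as a difference in change; of the listed tests only the mixed ANOVA addresses change over time, and it is the analysis that takes covariates. The t tests could then be supportive, and error would be about 5% per population. This reading is reasonable, but the text does not make it: it lists the t tests first, without calling them supportive, and adds the ANOVA alongside. The ANOVA would also leave the time point open.

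A second reply is that a test hierarchy is often left to an analysis plan. That would answer a complaint about absent detail. Here the article itself defines the primary outcome without its time and sets competing analyses side by side, so what it does state is ambiguous.

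Three stronger readings are tempting, and the documents do not support them:

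- A reader might take 21–24% as the chance of falsely claiming benefit. That figure counts both directions and treats success in either population as one joint claim. The comparative hypothesis in the Aim section names patients and carers without saying whether either suffices. If they are separate claims, no cross-population figure applies; if both had to succeed, error with no effect in either would be small.
- A reader might treat the Aim section's mention of significant results as a decision rule. It is an aspiration about later work, and the Discussion states an expectation. Neither authorises whichever result succeeds to carry the conclusion.
- A reader might add the effect of allocation by centre. That is a separate issue, the documents give no intracluster correlation, and the figures here leave it out.

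**Conclusion.** The point holds as a matter of ambiguity with a measurable but moderate cost. Per population, the chance of at least one significant result under no effect is about 11–13% rather than 5%. In the intervention's favour it is about 6–7% rather than 2.5%. The second pair is the right one for a false claim of benefit. Over both populations the figures are 21–24% and 11–13%, and only under a joint claim that either population can satisfy.

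These rest on an inferred two-sided 5% level, the planned completers, the assumed correlations above, independent individuals, and any significant test being allowed to count. The problem should be corrected before quantitative analysis. It does not by itself undermine the design or Table 2.

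**What to change.** Before quantitative analysis, which Table 1 places in the last two periods of 2018, add one paragraph that:

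1. names one deciding contrast per population, matching the primary outcome: the baseline-adjusted arm difference in PDQ-39 for patients and in SQLC for carers, at one stated time point;
2. tests the other time point only if the first is significant, which keeps multiplicity error within the chosen level in each population;
3. makes the remaining t tests and the omnibus ANOVA descriptive;
4. states that patients and carers support separate claims, and states the significance level.

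The time point is the sponsor's choice. T1 matches the expected short-term effect. T2 addresses durability but is collected by post, which the Limitations section already flags.

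The cost is that one time point loses primary status; separate claims need no larger sample. Splitting alpha across the populations is optional and would lower power to roughly 70–73% at the planned size.
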